#### Composite pain score and opioid consumption (PIOC) score

Because opioids and other pain medications could also influence the pain score (interdependence), and to overcome key statistical challenges such as mass significance and increased risk of type 1 error, other researchers suggested a composite pain and opioid consumption (PIOC) score for analgesic clinical studies. We will apply the novel approach of this integrated outcome measurement by including longitudinally measured PIOC score over the 7-day follow-up period. The area under the curve for a child-reported overall pain (AUC-NRS) and morphine equivalent total dose of pain medications (AUC-OC) would be calculated by the trapezoidal rule. The trapezoidal rule estimates the AUC by summarizing the trapezoid areas under the graph between each pair of consecutive observations and then ranks AUC-NRS and AUC-OC for both VR and control groups. PIOC is the summation of the deviations from the mean ranks for both parameters and equals − 200% to + 200% for each patient. Effect size could then be expressed as the probability of having a better (lower) PIOC score with treatment compared to the control group. The *U* value from the Mann–Whitney *U* test will be used to calculate a “probability” (*P*′). The *P*′ could be applied in the estimation of a generalized odds ratio, which provides the effect size, including 95% CI. The generalized odds ratio can be interpreted as the probability of a randomly chosen patient in the intervention VR group having better ratings of the composite analgesic outcome than a randomly chosen patient in the control group. To the best of our knowledge, based on our review of the literature on VR studies, this innovative PIOC approach has not been used by other researchers in the assessment of the effectiveness of VR on pain score and opioid medication reduction. We have successfully applied this innovative pain outcome statistical test approach in our feasibility RCT study among 24 pediatric burn patients [20].

#### Aim 2

In the primary analysis, the mean child-reported VR engagement score in the VR-PAT group will be calculated along with a 95% confidence interval for each of the seven follow-up days. The intention-to-treat principle will again be used in the primary analysis by accounting for all subjects in the VR-PAT group in the calculation regardless of whether they actually use the VR device during dressing changes. Sensitivity analysis will also be conducted by imputing missing scores due to dropout and then recalculating the mean scores and their 95% confidence intervals. In the secondary analysis, the mean child-reported fun score and mean child-reported realism score will be calculated along with 95% confidence intervals for each of the 7 days. In addition, a linear mixed effect model with random intercept, dependent variable of child-reported VR engagement score, and independent variable of time will be fit to assess the trend of engagement score over the seven follow-up days. The coefficient of time will reveal the direction and magnitude of the trend. The same linear mixed effect models will be fit for child-reported fun scores and mean child-reported realism scores to assess their trends over time.

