### Sample size {14}

The sample size was calculated for the primary outcome of the child-reported overall pain score. We consider a 30% reduction in the pain NRS score as a minimal clinically meaningful reduction in pain. According to our previous publication on pain reduction of VR-PAT among pediatric patients 6–17 years of age who were treated at our outpatient burn clinic [19], the pooled standard deviation (SD) of the child-reported overall pain visual analog scale (VAS) score was estimated. Aiming at detecting a 30% reduction of the pain score in the VR-PAT group compared with the control group at any of the first 7 days of follow-up, and assuming the same SD on these days, we will need 89 subjects per group to achieve 80% power and a two-sided type-I error of 0.01 at each day using a two-sample *t*-test. The type-I error rate is adjusted by Bonferroni correction for multiple comparisons. Assuming a 10% dropout rate, we will need 99 subjects per group. Based on this calculation, we plan to *n* = 100 subjects per group (*n* = 200 subjects total).

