### Methods in analysis to handle protocol non-adherence and any statistical methods to handle missing data {20c}

The intention-to-treat principle will be used in the primary analysis, in that subjects will be analyzed according to their assigned study group regardless of whether they used the VR-PAT or in the control group during dressing changes. Subjects that drop out of the study will be excluded from analyses after their dropout date. As a sensitivity analysis, the missing pain scores due to dropout will be imputed by multiple imputations with chained equations, and two-sample *t*-tests will analyze the imputed dataset. For Aim 2, sensitivity analysis will be conducted by imputing missing scores due to dropout and then recalculating the mean scores and their 95% confidence intervals.

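### PIOC ranks undivided trapezoid areas, so a child who stops reporting early tends to rank as better, and unequal partial dropout would tilt the comparison towards the arm that loses more children

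*Protocol article*

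**What the plan says.** The PIOC section promises an integrated outcome, "including longitudinally measured PIOC score over the 7-day follow-up period". For the pain area (AUC-NRS) and the opioid area (AUC-OC) it gives this definition: "The trapezoidal rule estimates the AUC by summarizing the trapezoid areas under the graph between each pair of consecutive observations". The opioid part is described as "morphine equivalent total dose of pain medications (AUC-OC) would be calculated by the trapezoidal rule". Both areas are ranked across the two arms, and "PIOC is the summation of the deviations from the mean ranks for both parameters". The effect size is "the probability of having a better (lower) PIOC score with treatment compared to the control group", so a small area is a good result. The section has no division by observed time, no extension to day 7 and no minimum number of days.

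The missing-data section {20c} states: "Subjects that drop out of the study will be excluded from analyses after their dropout date". Its Aim 1 sensitivity analysis is that "the missing pain scores due to dropout will be imputed by multiple imputations with chained equations, and two-sample" t-tests are then run on the imputed data. Opioid doses and PIOC are not mentioned there.

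Hypothesis 1 under Objectives {7} is stated in terms of PIOC. The primary analysis under Aim 1 is a daily t-test of the child-reported overall pain score.

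**The concern.** Both areas are sums of non-negative pieces, so cutting a series short at its end can only lower the area or leave it unchanged. If the two rules are followed as written, a child observed for 3 or 4 days is ranked on a truncated area against children with 7-day areas. Leaving early then counts as less pain and less opioid use.

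This matters if early stopping differs between arms. Only VR children have a device-related reason to stop, and section {11b} lists withdrawal among their options. The trial is also open-label. On the measure that carries Hypothesis 1, a poorly tolerated headset could then look like an analgesic benefit.

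A smaller problem affects the dose. A trapezoid over daily doses counts the first and last day at half weight, so it does not return the total dose that the text names.

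**Working it through.** **The plan's own figures.** Sample size {14} says "Assuming a 10% dropout rate, we will need 99 subjects per group": 89 / (1 − 0.10) = 98.9, which rounds up to 99. The stated PIOC range also reproduces. With N = 200 the mean rank is 100.5, so the extreme is 2 × (200 − 100.5) / 100.5 = 198.0%, in line with ±200%. Neither figure is in dispute.

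**Truncated pain areas.** The area is the sum over consecutive days of (y_t + y_{t+1}) / 2.

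| Series | Area | Mean over observed days |
|---|---|---|
| NRS 4 on all 7 days | 6 × 4 = 24 | 4 |
| NRS 4, stops after day 4 | 3 × 4 = 12 | 4 |
| NRS 4, stops after day 3 | 2 × 4 = 8 | 4 |
| NRS 6, stops after day 4 | 3 × 6 = 18 | 6 |
| Falling evenly from 5 to 2 over 7 days | 21.0 | 3.5 |
| Same decline, stops after day 4 | 12.75 | 4.25 |

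The child at NRS 6 who stops after day 4 (18) ranks better than the child at NRS 4 who completes (24). A single observation gives an area of 0. A missing day inside the series is bridged, so only truncation at the end matters.

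**Dose.** Daily doses of 10, 8, 6, 4, 2, 0, 0 sum to 30. The trapezoid gives 9 + 7 + 5 + 3 + 1 + 0 = 25, that is 30 − 10/2 − 0/2. Ten units on day 1 only score 5, while six units on day 2 only score 3 + 3 = 6, so the order of the two totals is reversed.

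**Arm comparison with no treatment effect.** The article gives one overall dropout figure (10%) and no rate by arm, so the rates below are assumptions. The other assumptions are 90 per arm, child means N(4, 2), daily noise SD 1.5, scores clipped to 0–10, 30% opioid users, all dropouts stopping after day 3, and a Mann–Whitney test on the full composite at the 5% level. The generalized odds ratio is P' / (1 − P').

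| Dropout, VR vs control | P' | Generalized OR | Rejection |
|---|---|---|---|
| 15% vs 5% | about 0.53 | 0.53/0.47 = 1.13 | about 11% |
| 20% vs 5% | about 0.55 | 0.55/0.45 = 1.22 | 20–23% |

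The pain component alone gives larger figures (P' 0.54 and 0.56, with rejection of about 15% and 27–30%). Those should not be quoted for PIOC, because children without opioids stay tied at zero whatever their follow-up.

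**Sensitivity to the assumptions.**
- Half of the dropouts return no surveys: rejection falls to roughly 6–11% across the two contrasts.
- Last observed day spread over days 2 to 6, 100 per arm: 15% vs 5% gives P' 0.523 and about 8% rejection.
- Equal 10% dropout in that same model: P' 0.50 and about 4% rejection, although dropouts average a PIOC of −53% and completers +6%.

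**The obvious repair.** Dividing each area by observed time returns P' to about 0.50 when pain is flat. When pain falls by 0.5 NRS per day, it over-corrects: at 20% vs 5% P' is about 0.48.

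**The case against.** The best defence is that the article never says what happens to an incomplete series. It names a 7-day period, describes the trapezoidal rule in general terms, and could leave scaling or minimum days to an analysis plan that is not shown. The dropout sentence suits daily t-tests and a mixed model. For a one-number summary it might mean that a dropout has no area at all. This has some force, but the article does fix both the area formula and the dropout rule, and following them literally gives the truncated ranking. The concern rests on those stated rules, not on silence.

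The design also limits the mechanism, and this part of the objection stands. Surveys are kept in a folder and normally returned together after the week, so many dropouts may supply nothing and have no area to rank. Sections {11b} and {22} let a child who cannot tolerate the headset carry on with dressing changes without it, and {11b} extends this to the surveys. The half weight on the first and last dose applies equally to both arms and creates no arm bias under the null.

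A reader might infer that PIOC is bound to favour VR, or that the trial's main result is compromised. The documents support neither. They give no dropout rate by arm, and equal non-informative dropout leaves the comparison unbiased. The primary t-tests do not use PIOC. The planned mixed model also gives an overall pain comparison from all observed days without this truncation. Nor does every dropout rank well: one with high pain can still rank worse than a completer with low pain.

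**Conclusion.** The concern holds in a bounded form. As written, PIOC gives a child with a short returned series smaller areas than the same child would have over 7 days, and smaller counts as better. The arms are biased only if partial dropout is unequal or informative, and then towards the arm with more of it. Under the stated assumptions the null P' moves from 0.50 to about 0.53 at 15% versus 5%, or about 0.55 at 20% versus 5%, with rejection of about 11% and 20–23%. These are illustrations: the dropout imbalance, the share of opioid users and the stopping day are all assumed, and later stopping or unreturned surveys reduce the effect.

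The point should be settled before analysis because Hypothesis 1 is worded on PIOC. It does not threaten the primary analysis. The dose point is a mismatch between the formula and the quantity named, and is minor.

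**What to change.** 1. Compute PIOC for every child on a common 7-day window. Extend the multiple imputation already planned for pain scores to daily pain scores and daily morphine equivalents together, build PIOC within each imputed data set, and pool the effect estimate.
2. Report areas per observed day as a sensitivity analysis only, because that version is biased the other way when pain declines over the week.
3. Treat days after dressing changes have ended separately from dropout days, and state how they enter the area. Eligibility {10} expects daily changes for about 5 days, whereas Table 1 plans 7 questionnaires.
4. Use the sum of daily morphine equivalents for the opioid part instead of a trapezoid.
5. State how families who return no surveys are handled, and report the number of days observed by arm.

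The cost is revised wording, a little more analysis work and reliance on the imputation model, which will be least certain for doses with many zeros. No new data are needed, and the article reports recruitment as still under way, so the change can be made before analysis.

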### Eligibility criteria {10}

Eligibility will be assessed using the following criteria: (a) undergoing treatment for acute burn injury; (b) age 6–17 years, inclusive; (c) receiving their first outpatient clinic dressing change or being discharged from the ED or inpatient burn unit; (d) having a dressing that requires daily changes at home for about 5 days after their first outpatient appointment or discharge from the hospital; (e) patient and family caregivers can communicate (read and write) using English or Spanish; and (f) report an NRS pain score of ≥ 1 (NRS 0–10 with 10 being worst pain) from the most recent dressing change. To minimize the possibility of confounding variables, the following exclusion criteria will be applied: (a) any wounds that may interfere with study procedures (i.e., face burns); (b) vision, hearing, or cognitive/motor impairments preventing valid administration of study measures; (c) history of motion sickness, seizure disorder, dizziness, or migraine headaches precipitated by visual auras; (d) minors in foster care, prisoners, or those who are currently pregnant; (e) suspected child abuse; (f) unable to communicate in English or Spanish; and (g) families who do not have access to a VR compatible smartphone.

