### Criteria for discontinuing or modifying allocated interventions {11b}

VR intervention group participants will be advised to discontinue using the headset during a dressing change if it causes motion sickness, headaches, nausea, or dizziness. Participants are welcome to try using the headset again for the next change but have the option of continuing the dressing changes and surveys without it or withdrawing from the study. Any adverse events from participation will be noted and reported on the subject surveys.

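### PIOC ranks AUCs that grow with the number of days recorded, so a partial record earns a better rank, and the comparison is biased if partial records differ between arms

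*Protocol article*

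**What the plan says.** The section on the composite PIOC score (Protocol article) describes "including longitudinally measured PIOC score over the 7-day follow-up period". Its pain component is the AUC of the child-reported overall score. Its opioid component is given as "morphine equivalent total dose of pain medications (AUC-OC) would be calculated by the trapezoidal rule". The rule for both is: "The trapezoidal rule estimates the AUC by summarizing the trapezoid areas under the graph between each pair of consecutive observations". The two AUCs are then ranked over both groups, and "PIOC is the summation of the deviations from the mean ranks for both parameters". The effect size is "the probability of having a better (lower) PIOC score with treatment compared to the control group", taken from the Mann–Whitney U.

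Three other sections decide how long a child's curve is:

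- Section {20c}, on non-adherence and missing data: "Subjects that drop out of the study will be excluded from analyses after their dropout date". Its imputation for Aim 1 is a sensitivity analysis of missing pain scores, analysed by two-sample t-tests. It covers neither opioid dose nor PIOC.
- Eligibility criteria {10}: a child qualifies by "having a dressing that requires daily changes at home for about 5 days", while PIOC is described over seven days.
- Section {11b}: children in the VR arm who feel unwell with the headset "have the option of continuing the dressing changes and surveys without it or withdrawing from the study".

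Sample size {14} assumes 10% dropout and gives no split by arm.

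**The concern.** A trapezoid sum is a total, and a total grows with the number of days it covers. Ranking totals of unequal length mixes how much pain a child had with how long the child was observed. Because lower is better, the error always favours the shorter record.

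PIOC is the measure named in Hypothesis 1, and its P′ and generalized odds ratio are the planned effect size for pain and opioid use together. Intention-to-treat does not help, because the child stays in the assigned arm with a shortened AUC. If early withdrawal after simulator sickness leaves more partial records in the VR arm, part of any apparent VR benefit on PIOC would come from missing days.

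**Working it through.** **Check on the reading of the score.** With 200 ranked children the mean rank is 100.5. The extreme deviations are (1 − 100.5)/100.5 = −99.0% and (200 − 100.5)/100.5 = +99.0%. Two components give about −198% to +198%, in line with the stated −200% to +200%. So the ranks are pooled over both arms and expressed relative to the mean rank, and the AUCs themselves are what is ranked.

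**Effect of record length.** With k daily scores at a constant level c, the trapezoid sum is c × (k − 1).

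- At c = 5: k = 7 gives 5 × 6 = 30; k = 5 gives 5 × 4 = 20; k = 3 gives 5 × 2 = 10.
- To tie with a 7-day child at pain 4 (AUC 24), a 5-day child needs 24/4 = 6, a 4-day child 24/3 = 8, and a 3-day child 24/2 = 12, which is above the scale maximum of 10.

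**Simulation with no true effect.** The procedure followed the text: trapezoid to the last recorded day, both AUCs ranked, deviations summed, Mann–Whitney test at two-sided 5%, P′ = probability that VR is better. There were 100 children per arm and 2,000 runs. Assumptions not in the documents: integer NRS with mean 4 on day 1 falling 0.3 per day, between-child SD 1.6, within-child SD 1.2, 30% opioid users, dropouts last seen on days 2 to 6, dropout unrelated to pain.

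| Partial records, VR vs control | As written: P′, false positives | Divided by time covered: P′, false positives |
|---|---|---|
| Dropout 10% vs 10% | 0.500, 4.2% | 0.499, 4.2% |
| Dropout 15% vs 5% | 0.523, 9.2% | 0.494, 5.7% |
| Dropout 20% vs 0% | 0.545, 19.6% | 0.489, 5.6% |
| Dropout 30% vs 10% | 0.544, 18.5% | 0.487, 6.1% |
| Dropout 5% vs 15% | 0.478, 7.5% | 0.506, 4.8% |
| 5-day course 30% vs 30% | 0.501, 4.6% | 0.501, 3.9% |
| Dropout 20% vs 0%, flat pain | 0.555, 26.1% | 0.500, 4.2% |

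P′ of 0.545 is a generalized odds ratio of 0.545/0.455 = 1.20 where the truth is 1. With the imbalance reversed, the bias favours control.

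**Sensitivity to the assumptions.** With slope −0.25 per day, within-child SD 1.5, 40% opioid users and dropouts leaving after 2 to 4 recorded days, false positives are 33% at 20% vs 0%, 22% at 20% vs 5% and 11% at 15% vs 5%. Over all assumption sets tried, the range is 20 to 39% at 20% vs 0% and 9 to 14% at 15% vs 5%. At 12% vs 8% it is 5 to 6%. At 15% vs 5%, if half of the dropouts return nothing and so are not ranked, it is 5.0%.

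**Power when loss is balanced.** With a true 25% pain reduction, 10% loss in each arm and 5 to 7 days of changes, power was 75% as written against 83% after dividing by time in one set of assumptions, and 60% against 69% in another. Over all sets the cost was about 8 to 13 points.

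**The case against.** **The rule is partly inferred.** The article never says that a curve stops at the last recorded day, and handling of incomplete curves is often left to an analysis plan. That is fair as to wording. But the article does state the summation rule, the ranking and the removal of data after dropout, and following those three statements gives this result.

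**Short courses do not bias the comparison.** A reader might infer that admitting children with about 5 days of changes favours one arm. The documents do not support that. The clinician settles the dressing before the family is approached (Recruitment {15}), without research influence (Implementation {16c}), and randomisation follows consent and the baseline survey (Concealment mechanism {16b}). Short courses should balance, and then only precision suffers.

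**Simulator sickness is not automatically a VR success.** A reader might infer that every child who stops the headset is scored as an analgesic success. Sections {11b} and {22} let such a child carry on with dressing changes without it, and {11b} says the surveys continue too; that child keeps a full curve. Withdrawal is open to both arms. A child who does leave early is ranked better than if fully observed, but not necessarily well.

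**Much of the expected loss is harmless here.** Surveys come back as a packet, and a family that returns nothing has no AUC. Mid-week gaps are bridged by the trapezoid. A child with no opioid use has a zero opioid AUC at any length, so that component shifts only among users.

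**A smaller total may be real.** If dressing changes truly end early, total burden is lower. That is a legitimate target, but the plan should then say so, and it would not justify truncation by dropout.

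**PIOC is not the primary analysis.** The daily t-tests are, and the mixed model uses the available days without this fault. This limits the consequences to PIOC and to the part of Hypothesis 1 that rests on it.

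**Conclusion.** The point holds in a conditional form. As written, PIOC gives a partial record a better rank than the same child would have with a full one; this is arithmetic and needs no assumption. Bias between arms arises only if partial records are unequally common. Its size then depends on inputs that the documents do not give (pain level and trend, SDs, opioid use, when dropouts leave, and the split by arm): negligible to small at 12% vs 8%, about double the nominal error or more at 15% vs 5%, and several times nominal at 20% vs 0%.

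A reader might take the 20 to 39% figures as this trial's expected error rate. They are not: they belong to lopsided loss, the upper values to dropouts who leave early in the week, and the protocol assumes only 10% dropout without saying how it divides. With balanced loss there is no bias, only a power cost of roughly 8 to 13 points under the assumed inputs. The plan should be changed, because the stated rule is the weaker one and a better one is readily available.

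**What to change.** In the section on the composite PIOC score, divide each child's AUC-NRS and AUC-OC by the time covered before ranking, and state that PIOC measures burden per dressing-change day. Say also what is done with a child who has only one recorded day, since the time covered is then zero.

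As a sensitivity analysis, extend section {20c}: multiply impute both daily pain and daily morphine-equivalent dose for days lost to dropout, and repeat PIOC in the imputed data sets. The present text imputes pain only, so PIOC cannot be rebuilt from it. Days after a course of dressing changes has ended as planned are not lost to dropout and should not be imputed.

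The division costs one sentence and a few lines of code. The imputation costs more, because opioid dose must be added to the model. One small downside remains: when pain falls over the week, an early leaver's average comes from the more painful first days, so time-averaging slightly penalises the arm with more dropout (P′ about 0.49 instead of 0.50). The imputed version addresses this.
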